### Interventions

2.4

Participants will be randomly assigned to receive anti-TB drugs in either the short-course regimen or the empirical long-course regimen. Participants in the short-course regimen group will receive 8 weeks of daily treatment with isoniazid, rifapentine, pyrazinamide and moxifloxacin, followed by 18 weeks of daily treatment with isoniazid, rifapentine, and moxifloxacin (2HRtZM/4HRtM). Participants in the empirical long-course regimen group will receive 8 weeks of daily treatment with rifampin, isoniazid, pyrazinamide, and ethambutol, followed by 44 weeks of daily treatment with rifampin and isoniazid (2RHZE/10RH). All drugs will be administered orally once daily. The dosing regimen details are provided in Table 3.

**TABLE 3 T3:** Dosing regimens.

Group	Medicine	Dosage		Durations
Short-course regimen (2HRtZM/4HRtM)	Rifapentine	≤41.2 kg	750 mg	26 weeks
		>41.3–48.7 kg	900 mg	
		>48.8–56.2 kg	1,050 mg	
		≥56.3 kg	1,200 mg	
	Moxifloxacin	400 mg		26 weeks
	Isoniazid	300 mg		26 weeks
	Pyrazinamide	<55 kg	1,000 mg	8 weeks
		≥55–75 kg	1,500 mg	
		>75 kg	2000 mg	
Empirical long course regimen (2RHZE/10RH)	Rifampin	600 mg		52 weeks
	Isoniazid	300 mg		52 weeks
	Pyrazinamide	<55 kg	1,000 mg	8 weeks
		≥55–75 kg	1,500 mg	
		>75 kg	2000 mg	
	Ethambutol	<55 kg	800 mg	8 weeks
		≥55–75 kg	1,200 mg	
		>75 kg	1,600 mg	

All drugs are administered orally, once a day.

### Data collection

2.5

Participants will undergo clinical and laboratory assessments at predetermined timepoints (Table 4). In addition, to evaluate the exposure levels of anti-TB drugs in the body of participants, pharmacokinetic samples, including but not limited to blood, will be collected by using an opportunistic sampling method (Leroux et al., 2015). The samples will be collected at any time after the 14th dose of the anti-TB drugs, but no later than Week 8 after the start of treatment. Collection is recommended at weeks 2, 4, and 8. A total of 2-4 blood samples will be collected from each participant during the entire treatment period. The study follow-up will continue for 24 months after the completion of anti-TB treatment.

**TABLE 4 T4:** The schedule of study assessments for this trial.

Visit	Baseline period	Treatment period ( ± 3 days)							Follow-up period ( ± 7 days)						Possible poor treatment response	Post early termination visit
Timing	-7days - 0 d	WK 2	WK 4	WK 8	WK 13	WK 17	WK 22	WK 26	MO 9	MO 12	MO 18	MO 24	MO 30	MO 36		
Informed consent	X															
Inclusion/Exclusion	X															
Randomization	X															
Demographics	X															
Contact information	X	X	X	X	X	X	X	X	X	X	X	X	X	X	X	X
Medical history and diagnosis	X															
Symptoms		X	X	X	X	X	X	X	X	X	X	X	X	X	X	X
Administration		X	X	X	X	X	X	X								
Concomitant medications		X	X	X	X	X	X	X	X	X	X	X	X	X	X	X
Recent medical record									X	X	X	X	X	X	X	
Height	X															
Weight	X	X	X	X	X	X	X	X	X	X						
Diabetes screening	X															
Visual tests			X													
Pregnancy testing	X															
Rapid molecular test	X															
Bacterial smear and culture	X	X	X	X	X	X	X	X	X	X	X	X	X	X	X	
Chest radiograph	X							X		X						
Neurological assessment	X	X	X	X	X	X	X	X	X	X	X	X	X	X	X	
Biochemical test	X	X	X	X	X	X	X	X	X	X						X
Blood tests	X	X	X	X	X	X	X	X	X	X						X
PK sampling		X	X	X												
Adverse events		X	X	X	X	X	X	X	X	X	X	X	X	X	X	X
CRF	X	X	X	X	X	X	X	X	X	X	X	X	X	X	X	X

X Fixed. PK, pharmacokinetics; CRF, case report form.

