#### Primary outcomes

2.6.1

The primary outcomes are TB-recurrence rate of spinal tuberculosis at 24 months after completion of treatment (efficacy outcome, non-inferiority aspect) and the proportion of participants with grade 3 or higher adverse events (AEs) during study medication (safety outcome, superiority aspect). The recurrence of spinal tuberculosis is defined by the reappearance of pain, with or without sinus formation, loosening or displacement of internal fixation on X-ray, and confirmed by postoperative computed tomography or magnetic resonance imaging showing increased local abscess, bone graft absorption, new sequestrum formation, or aggravated bone destruction (Ren et al., 2016). AEs are graded per CTCAE v5.0, with grade 3+ events defined as severe functional impairment, life-threatening complications, or death; causality is adjudicated by the Safety Monitoring Committee using WHO-UMC criteria.

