### Sample size

2.7

We estimated the sample size based on the non-inferiority hypothesis that the TB-recurrence rate of spinal tuberculosis at 24 months after completion of treatment of the short-course regimen will be no worse than the empirical long-course regimen. It is assumed that the TB-recurrence rate in the empirical long-course group is 5% and the rate will be the same in the short-course regimen arm. Considering a 10% dropout rate, a sample size of 150 per arm (300 in total) will give 80% power (one-sided type I error of 5%) to demonstrate a 6.6% non-inferiority margin (Dorman et al., 2021) using Pearson chi-square test with normal approximation. Detailed sample size calculation steps, including the statistical formula, parameter justification, and sensitivity analysis results, are provided in the Supplementary Material.

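### Table 4 schedules the only visual test at week 4, with none before dosing, so a previously unknown deficit found then cannot be reliably classed as old or new

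*Protocol article*

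**What the plan says.** Section 2.5 of the protocol article ties assessments to its schedule: "Participants will undergo clinical and laboratory assessments at predetermined timepoints (Table 4". Table 4 prints that schedule in full, and its footnote describes the marks as fixed. The visual tests row has one mark, under week 4. The cells for baseline (day -7 to day 0), week 2, week 8 and every later visit are empty.

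Section 2.4 gives the long-course arm "8 weeks of daily treatment with rifampin, isoniazid, pyrazinamide, and ethambutol" before its continuation phase. The short-course arm receives no ethambutol.

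Section 2.6.1 names as the safety primary outcome "the proportion of participants with grade 3 or higher adverse events (AEs) during study medication (safety outcome, superiority aspect". It adds that "AEs are graded per CTCAE v5.0" and that "causality is adjudicated by the Safety Monitoring Committee using WHO-UMC criteria".

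The article does not say what the visual test consists of or why it is done.

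**The concern.** A single on-treatment reading shows a participant's vision about four weeks into dosing. It does not show whether vision has changed. If week 4 reveals a deficit that the participant did not know about, there is no earlier measurement to compare it with.

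Two wrong decisions become possible. A long-standing deficit may be taken for a drug effect and treatment stopped without need, or a real decline may be dismissed as old. Roughly half of the ethambutol course is still to run at that visit, so the reading can still affect treatment.

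The same gap reaches the Safety Monitoring Committee, which would judge the cause of a visual event first seen at week 4 without a scheduled pre-dose test. Allocation is open, which makes an objective reference value more useful.

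**Working it through.** The point concerns a schedule, so most of the check is a reading of Table 4.

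**1. Is the week 4 reading of the row reliable?** Table 4 has 24 rows, each with 16 cells: 1 baseline, 7 treatment visits, 6 follow-up visits, 1 for possible poor response and 1 for early termination. The visual tests row has its only mark in cell 3, which is week 4. As an alignment check, the pharmacokinetic sampling row is marked in cells 2, 3 and 4 (weeks 2, 4 and 8), and the text of section 2.5 independently says: "Collection is recommended at weeks 2, 4, and 8". The columns are aligned, so the empty baseline cell is not an extraction artefact.

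**2. Does anything else supply a pre-dose visual value?**

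| Possible source | What it can show |
|---|---|
| Medical history at baseline (Table 4) | Only a deficit already known |
| Exclusion criterion 13, investigator's judgment (Table 2) | Only a deficit already known |
| Other eligibility criteria (Table 2) | None concerns vision |
| Neurological assessment at baseline (Table 4) | Not described as covering vision |
| Symptoms row (Table 4) | Starts at week 2 |
| Adverse event recording (Table 4 from week 2; section 2.10 from consent) | Only what is noticed or reported |

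None gives a measured reference for a deficit that the participant has not noticed.

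**3. Does the empty cell fit the table's own pattern?** Seven examinations or tests are marked at least once in weeks 2 to 26 and could have a pre-dose value: weight, smear and culture, chest radiograph, neurological assessment, biochemistry, blood tests and visual tests. Six of the seven have a baseline mark; the visual test is the exception. Pharmacokinetic sampling is left out because it is post-dose by design. Record and enquiry rows are left out because they are not tests.

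**4. Could the week 4 reading stand in for a baseline?** Week 4 is day 28. With the treatment-period window of ±3 days, the reading falls between 28 − 3 = day 25 and 28 + 3 = day 31, after more than three weeks of daily dosing. It cannot. Ethambutol ends at week 8 (day 56), so 56 − 31 = 25 to 56 − 25 = 31 days of it remain.

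**5. How many visits and participants are involved?** Of the four scheduled visits up to the end of ethambutol (baseline and weeks 2, 4 and 8), one has the test, and it is not the pre-dose visit. The head count comes from section 2.7, which reproduces. With 5% recurrence in both arms, a 6.6% margin, one-sided 5% error and 80% power:

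n = (1.645 + 0.842)² × 2 × 0.05 × 0.95 / 0.066² ≈ 134.8, rounded up to 135 per arm; 135 / (1 − 0.10) = 150 per arm, 300 in total.

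The concern uses this figure only as a count. As scheduled, 300 participants have no pre-dose visual value, and 150 of them are assigned ethambutol.

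**6. Does it reach the outcome comparisons?** As worded, the adverse event outcomes are not counted by attribution, and the visual tests row applies to both arms. No material effect on the primary or secondary comparisons follows.

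**The case against.** The strongest reply is that Table 4 is condensed and that an empty baseline cell there does not prove that nothing was assessed before dosing. Symptoms and concomitant medications also lack a baseline mark, yet the eligibility criteria require clinical manifestations and prior drug treatment to be checked. Performance status is an entry criterion and has no row. The full protocol may contain a baseline eye test. If those two enquiry rows are counted, the pattern is 6 of 9 rather than 6 of 7, and the visual test is no longer the sole exception.

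The reply also notes that neither the purpose nor the type of test is stated, that half the participants never receive ethambutol, that the number affected is unknown, and that no outcome effect is claimed.

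Part of this stands. The 6 of 7 count depends on restricting it to tests and is supporting evidence only. The purpose is an assumption. If it concerns ethambutol specifically, the 150 in the long-course arm are the relevant group.

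The rest does not remove the problem. The pre-dose content of the two enquiry rows is covered by history and eligibility checks; a visual measurement is covered by neither. The row is present, its timing is fixed, and its baseline cell is empty, which differs from a detail left out of an article. If the full protocol does include a baseline test, the published table is wrong and needs the same one-cell correction.

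**Conclusion.** The concern holds. Table 4 provides one visual test, at week 4, and no pre-dose reference, so a previously unknown deficit found there cannot be reliably classed as pre-existing or new. Later symptom, neurological and adverse event enquiry may settle some cases but does not replace the missing measurement.

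The conclusion rests on one stated assumption: that the test is there to detect drug-related visual change. The natural support for this is that the test is done only on treatment, midway through the ethambutol phase.

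The consequence is limited to individual safety decisions and case-level causality adjudication. The number of participants with an unrecognised deficit cannot be derived from the article. The change is recommended because it is cheap and the lost value cannot be recovered. The validity of the trial's comparisons does not depend on it. Confidence is moderate, since the full protocol is not shown.

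**What to change.** In Table 4, mark the existing visual test at the baseline visit, before the first dose, in both arms. State that the week 4 result is to be judged against the participant's own baseline. A week 8 mark is optional: it would document late change but could not guide stopping ethambutol, which ends that week.

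The cost is one added mark and 300 × 1 = 300 further tests, 150 per arm, at a visit already held and using a test the sites already perform at week 4. Half of these fall in the arm without ethambutol, but the existing row already covers both arms. The article does not name the test, so the cost per test is not known. The change helps a participant only if it is in force before that participant's first dose.

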### Outcomes

2.6

#### Primary outcomes

2.6.1

The primary outcomes are TB-recurrence rate of spinal tuberculosis at 24 months after completion of treatment (efficacy outcome, non-inferiority aspect) and the proportion of participants with grade 3 or higher adverse events (AEs) during study medication (safety outcome, superiority aspect). The recurrence of spinal tuberculosis is defined by the reappearance of pain, with or without sinus formation, loosening or displacement of internal fixation on X-ray, and confirmed by postoperative computed tomography or magnetic resonance imaging showing increased local abscess, bone graft absorption, new sequestrum formation, or aggravated bone destruction (Ren et al., 2016). AEs are graded per CTCAE v5.0, with grade 3+ events defined as severe functional impairment, life-threatening complications, or death; causality is adjudicated by the Safety Monitoring Committee using WHO-UMC criteria.

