Anti-tuberculosis (anti-TB) drug therapy is a crucial approach for treating spinal tuberculosis infections, especially in cases of mild spinal tuberculosis (Rajasekaran and Khandelwal, 2013). In guidelines, an extended treatment duration of 9–18 months for osteoarticular tuberculosis is recommended, which is 1.5–3 times longer than the standard 6-month regimen (2HRZE/4HR) typically used for extrapulmonary tuberculosis (Hongqi et al., 2022; WHO, 2022). Beyond the direct health hazards of the diease itself, this prolonged treatment brings additional societal and economic burdens: it increases the risk of drug toxicity (such as hepatotoxicity) (Yew et al., 2018; Maiwall et al., 2024), drug resistance (Zumla et al., 2014) — a growing concern globally as multidrug-resistant TB continues to thwart control efforts (Romano et al., 2020) — and poor patient adherence (Guix-Comellas et al., 2015). These issues not only reduce treatment effectiveness but also lead to increased medical costs and resource comsumption; for patient in low- and middle-income regions or with limited medical access, the long treatment cycle may result in treatment interruption, further worsening the diease burden (Tochukwu et al., 2023).

A pilot study initially explored the efficacy of 6-month and 12-month anti-TB treatments for spinal tuberculosis, showing similar clinical outcomes in both groups (Nene et al., 2019). In addition, a large multicenter randomized controlled trial demonstrated that a new 4-month anti-TB regimen containing isoniazid, rifapentine, moxifloxacin, and pyrazinamide was non-inferior to the standard 6-month regimen (2HRZE/4HR) in treating drug-sensitive pulmonary tuberculosis in terms of efficacy, safety, and tolerability—confirming the synergistic bactericidal potential of these four drugs (Dorman et al., 2021). These findings, combined with the unique pharmacological advantages of rifarentine and moxifloxacin in targeting spinal tuberculosis, provide critical insights into optimizing treatment for mild spinal tuberculosis.

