### Randomization

2.3

A blocked randomization approach with stratification will be employed to allocate eligible patients into the short-course regimen [6-month anti-TB regimen] group and the empirical long-course regimen [12-month anti-TB regimen] group in a 1:1 ratio. The participants will be stratified according to the study sites. All research staff will undergo uniform training to ensure consistency across all study sites. The randomization list will be generated using SAS v9.4, and the allocation sequence will be carried out by the trial statistician via the central phone system. Both participants and investigators will be aware of the allocation, as the study will not be blinded.

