### Statistical analysis

2.9

The statistical analyses will be carried out in SAS v9.4 by independent statisticians. Descriptive statistical analysis will be performed by calculating the mean ± SD, median (minimum-maximum, or lower quartile-upper quartile) for continuous variables and counts (percentages) for categorical variables. The statisticians will perform chi-square test or Fisher’s exact test for categorical variables and Student’s test or Wilcoxon rank sum test for continuous variables. It will be considered statistically significant if p value <0.05. The efficacy analysis will use intention-to-treat, per-protocol, and as-treated populations. The concentration of anti-TB drugs will be determined using a validated LC-MS method at the Center for Pharmaceutical Analysis and Testing, School of Pharmaceutical Sciences, Shandong University. NONMEM 7.4 will be used to determine whether the PD targets have been achieved for each participant. Detailed statistical analyses are provided in the Supplementary Material.

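### The primary efficacy event has no place for added anti-TB drugs or spinal surgery, so a failure treated before it is documented can count as recurrence-free and favour non-inferiority

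*Protocol article*

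**What the plan says.** The protocol article's Primary outcomes section (2.6.1) builds the efficacy event from two parts. The clinical part reads: "The recurrence of spinal tuberculosis is defined by the reappearance of pain, with or without sinus formation, loosening or displacement of internal fixation on X-ray". The event must also be "confirmed by postoperative computed tomography or magnetic resonance imaging showing increased local abscess, bone graft absorption, new sequestrum formation, or aggravated bone destruction". Nothing in the definition refers to treatment received.

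Other places bear on this:

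- **Randomization (2.3):** "Both participants and investigators will be aware of the allocation, as the study will not be blinded".
- **Interventions (2.4):** assigned treatment ends at week 26 in the short arm and week 52 in the long arm.
- **Introduction:** for guideline practice, "an extended treatment duration of 9–18 months for osteoarticular tuberculosis is recommended".
- **Data collection (2.5), Table 4:** there is a visit column headed "Possible poor treatment response". Concomitant medications are recorded to month 36, and recent medical records from month 9 to month 36. No text links any of these to the primary outcome.
- **Secondary outcomes (2.6.2):** clinical cure at end of therapy and discontinuation of assigned treatment are listed, as secondary outcomes only.
- **Statistical analysis (2.9):** "The efficacy analysis will use intention-to-treat, per-protocol, and as-treated populations". The article does not say how any of the three treats a rescued participant.

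**The concern.** The trial asks whether six months of treatment is enough. A short-course participant who needed further anti-TB drugs or an operation for spinal TB has not shown that it is. Yet if the added treatment prevents or pre-empts pain with imaging change, that participant contributes a success. The same scoring applies in the long arm.

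In a superiority trial, rescue of this kind usually makes success harder to show. In a non-inferiority trial it works the other way: hidden failures shrink the observed difference against a fixed margin. The word for reappearance of pain adds to the problem. It presupposes that pain had resolved, so persistent disease that is simply treated onward also falls outside the event.

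At stake is the headline conclusion. The trial could find six months sufficient partly because some participants received more than six months.

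**Working it through.** **Inputs from the protocol (Sample size, 2.7).** The planning assumption is that "the TB-recurrence rate in the empirical long-course group is 5% and the rate will be the same in the short-course regimen arm". The margin is 6.6 points, one-sided alpha 5%, power 80%, dropout 10%, and 150 per arm.

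**Step 1: reproduce the plan's figure.** n per arm = (1.645 + 0.842)² × 2 × 0.05 × 0.95 / 0.066² = 134.8, rounded up to 135. Inflating for dropout, 135 / 0.90 = 150. The stated sample size is correct.

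**Step 2: set up the decision rule.** Two independent binomials with 135 per arm were enumerated exactly. Non-inferiority is declared when the difference (short minus long) plus 1.645 × SE is below 0.066, with SE = √[p_S(1 − p_S)/135 + p_L(1 − p_L)/135] from the observed proportions.

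- At 5% v 5% the power is 80.5% (normal approximation 80.0%).
- With the truth exactly at the margin, 5% + 6.6 = 11.6% v 5%, the chance of declaring non-inferiority is 5.9%. This is the baseline false-positive rate.
- Expected short-arm failures are 135 × 0.116 = 15.7.

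**Step 3: mask a fraction f of failures.** The observed short-arm rate becomes 11.6% × (1 − f). The long-arm rate becomes 5% × (1 − f) under equal masking, or stays at 5% if only the short arm is masked. The values of f are assumptions.

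| f | Short-arm failures hidden | Equal masking: observed difference | Equal masking: false non-inferiority | Short arm only: observed difference | Short arm only: false non-inferiority |
|---|---|---|---|---|---|
| 0 | 0 | 6.60 points | 5.9% | 6.60 points | 5.9% |
| 10% | 1.6 | 5.94 points | 8.9% | 5.44 points | 11.3% |
| 25% | 3.9 | 4.95 points | 16.3% | 3.70 points | 26.3% |
| 40% | 6.3 | 3.96 points | 29.0% | 1.96 points | 50.4% |

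Equal masking still inflates the error, because the difference becomes 6.6 × (1 − f) while the margin stays at 6.6. The direction therefore does not depend on rescue being unequal.

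**Step 4: allow for later documentation.** If half of the rescued short-arm participants later meet the definition, the effective f halves. The short-arm-only figures become 8.2%, 13.2% and 20.3%.

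**Step 5: price the remedy (same enumeration, true recurrence 5% in both arms).**

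| Points added by the wider endpoint | Power if added to both arms | Power if added to the short arm only |
|---|---|---|
| 0 | 80.5% | 80.5% |
| 1 | 74.6% | 65.8% |
| 2 | 69.4% | 49.8% |
| 3 | 64.8% | 35.0% |

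By the formula in Step 1, restoring 80% power for the both-arms case, with 10% dropout, takes 179, 206 or 233 per arm.

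**The case against.** **The article does not say in words that a rescued participant is recurrence-free.** It refers detailed analyses to Supplementary Material that is not shown. That limits certainty: an unseen rule could classify these participants. But the endpoint is defined in full in the article, the outcome section defers nothing, and the literal reading gives the anti-conservative result.

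**Per-protocol and as-treated analyses are also planned.** They may separate participants who deviate from assignment. No stated rule, however, makes such a participant a failure in any of the three populations.

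**Some failures would be visible elsewhere.** A participant with residual symptoms at the end of therapy could miss clinical cure, and discontinuation is tabulated. Both outcomes are secondary and neither feeds the non-inferiority decision.

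**A reader might infer that rescue would occur in the short arm only,** since that arm stops at month 6 while the other is still on assigned drugs. The documents do not support this. The cited 9–18 months also extends beyond the long arm's 12, and switching or surgery is possible in either arm throughout. No rescue rate or imbalance is given. The 50% figure needs 40% of failures to be masked permanently in one arm alone, so it is an upper scenario and not an expectation.

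**Counting every extension as failure could create the opposite bias.** Investigators know the allocation, and precautionary prescribing in the short arm would be scored as regimen failure. This objection stands, and it shapes the fix.

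**Conclusion.** The point holds for the endpoint as written. In either arm, a participant given non-assigned anti-TB drugs or spinal surgery for spinal TB before recurrence is documented, who never later meets the definition, is not an event under intention to treat. The bias favours non-inferiority, even when rescue is proportionally equal.

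Its size is conditional. With true rates at the margin and 135 evaluable per arm, false non-inferiority goes from 5.9% to about 9%, 16% or 29% with equal masking of 10%, 25% or 40%, and to 11%, 26% or 50% with short-arm masking only. The fractions are assumed, and participants documented with recurrence after rescue still count, which lowers these figures. It would go too far to conclude that rescue will be one-sided or that the trial's result will be wrong. The sample size calculation is sound for the rates it assumes. Severity: should-fix.

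**What to change.** In the primary outcome, classify as unfavourable any participant who, before the 24-month assessment and because of documented suspicion of persistent or recurrent spinal TB, either:

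- receives anti-TB drugs beyond or different from the assigned course, leaving out make-up of missed doses and changes made for toxicity; or
- has spinal surgery.

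Apply the rule identically in both arms. Report imaging-confirmed recurrence alone beside it, and require non-inferiority to be consistent on both before concluding that six months suffices.

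Identify cases from the concomitant-medication and recent-medical-record rows of Table 4, and add a field for the reason treatment was added. Table 4's row for study drug administration stops at week 26. A record of assigned dosing in weeks 27–52 of the long arm is therefore also needed, to tell make-up doses from extension.

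The costs should be stated openly. The event rate may exceed 5%, so the 80% power must be restated: about 75%, 69% or 65% if the wider endpoint adds 1, 2 or 3 points in both arms. Precautionary extension in the short arm could bias against non-inferiority, with power of about 66%, 50% or 35% if those points fall there alone. The reason requirement and the imaging-only result are kept for that reason. The change concerns how outcomes are classified, not what clinicians may give.

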## Introduction

1

Spinal tuberculosis is the most common type of osteoarticular tuberculosis, accounting for approximately 1%–3% of all tuberculosis cases and representing one of the most prevalent types of extrapulmonary tuberculosis (Meier, 1994; Li et al., 2023; WHO, 2024). As a country ranking third among the 30 countries with the highest tuberculosis burden globally, China faces considerable challenges from spinal tuberculosis, with a large number of new cases reported annually—its tuberculosis incidence reaching 52 per 100,000 population in 2023 (Li et al., 2023; WHO, 2023; WHO, 2024). Clinically, spinal tuberculosis poses severe health risks: it accounts for 62% of deaths associated with osteoarticular tuberculosis (Li et al., 2023), and post-tuberculosis sequelae such as spinal deformities, neurological disabilities, and paraplegia are common, significantly impairing patient’s quality of life and imposing long-term physical and psychological burdens (Igbokwe et al., 2023). For children and adolescents, these sequelae can lead to lifelong functional limitations, further exacerbating the public health impact (Igbokwe et al., 2023). Mild spinal tuberculosis, characterized by early-stage or localized spinal involvement (Oguz et al., 2008), constitutes a substantial proportion of spinal tuberculosis cases; these patients are primarily managed with drug therapy, which presents a unique opportunity to explore more optimized treatment strategies and to prevent further disease progression (Oguz et al., 2008).

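### The primary recurrence definition calls for postoperative imaging and surgical signs in a trial of drug treatment, and gives no rule for participants who were never operated on

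*Protocol article*

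**What the plan says.** Primary outcomes (section 2.6.1) says that recurrence is "defined by the reappearance of pain, with or without sinus formation". It then lists "loosening or displacement of internal fixation on X-ray" and requires the recurrence to be "confirmed by postoperative computed tomography or magnetic resonance imaging showing increased local abscess, bone graft absorption, new sequestrum formation, or aggravated bone destruction". No other definition of recurrence appears in the article.

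The rest of the article describes a population managed with drugs:

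- Introduction: of mild cases it says that "these patients are primarily managed with drug therapy".
- Interventions (section 2.4): "Participants will be randomly assigned to receive anti-TB drugs in either the short-course regimen or the empirical long-course regimen". All drugs are oral, and neither arm includes an operation.
- Table 1: entry is limited to disease with little vertebral collapse, limited abscess, no marked kyphosis and no apparent instability.
- Table 4: the only imaging row is "Chest radiograph". There is no row for spinal X-ray, CT or MRI.

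Sample size (section 2.7) assumes 5% recurrence in both arms, a margin of 6.6 percentage points, a one-sided 5% type I error and 10% dropout, and states that 150 per arm "will give 80% power".

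**The concern.** The definition presupposes an operation: a scan taken after it, a graft that can be absorbed and an implant that can loosen. The trial randomises to drugs, and most participants who satisfy Table 1 would be expected to have none of these. A participant with returning pain and a growing abscess on MRI, never operated on, has a recurrence in any ordinary sense but has no postoperative scan to confirm it.

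The site must then choose. It can apply the wording and record no event, or ignore the word and record one. The article does not say which, and the trial is open-label at 14 sites, so the choice can be made knowing the allocation.

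What is at stake is the non-inferiority conclusion. The margin is a fixed absolute difference. An event definition that misses true recurrences in both arms pulls the observed difference towards zero and makes non-inferiority easier to declare. Few events are expected, so a few missed ones matter.

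**Working it through.** **Inputs from Sample size (section 2.7).** Recurrence 5% in each arm; margin 0.066; one-sided alpha 0.05 (z = 1.645); power 80% (z = 0.842); dropout 10%.

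**Step 1: reproduce the stated sample size.**

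n = (1.645 + 0.842)² × 2 × 0.05 × 0.95 / 0.066² ≈ 134.8, so 135 evaluable per arm. Then 135 / 0.90 = 150, as stated. Expected recurrences are 135 × 0.05 = 6.75 per arm. The sample size is not in error.

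**Step 2: effect of under-counting, equal in both arms.** Let s be the share of true recurrences that the definition captures. The documents give no value for s; 0.75 and 0.50 are assumptions. Suppose the short course is worse by exactly the margin, with true rates 5% v 11.6%. The observed rates are 0.05s and 0.116s, and the observed difference is 0.066s. With 135 per arm:

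SE = √{[p₁(1 − p₁) + p₂(1 − p₂)] / 135}

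P(declare non-inferiority) = Φ[(0.066 − observed difference) / SE − 1.645]

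- s = 1: the difference equals the margin, so P = Φ(−1.645) = 5%.
- s = 0.75: rates 3.75% v 8.7%, difference 0.0495. SE = √[(0.0361 + 0.0794) / 135] = 0.0293. P = Φ(0.0165 / 0.0293 − 1.645) = Φ(−1.08) ≈ 14%.
- s = 0.50: rates 2.5% v 5.8%, difference 0.033. SE = √[(0.0244 + 0.0546) / 135] = 0.0242. P = Φ(0.033 / 0.0242 − 1.645) = Φ(−0.28) ≈ 39%.

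Exact binomial enumeration of the same Wald rule gives 5.9% at s = 1 and 41.7% at s = 0.50, so the normal approximation does not overstate the effect.

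Put another way, an observed difference of 6.6 points corresponds to a true difference of 6.6 / 0.75 = 8.8 points at s = 0.75, and 6.6 / 0.50 = 13.2 points at s = 0.50.

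**Step 3: unequal capture.** Same true rates, with 50% capture in one arm and full capture in the other:

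- Half captured in the short-course arm only: 5% v 5.8%, difference 0.008. SE = √[(0.0475 + 0.0546) / 135] = 0.0275. P = Φ(0.058 / 0.0275 − 1.645) ≈ 68%.
- Half captured in the long-course arm only: 2.5% v 11.6%, difference 0.091. SE = √[(0.0244 + 0.1025) / 135] = 0.0307. P = Φ(−0.025 / 0.0307 − 1.645) ≈ 0.7%.

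The direction towards non-inferiority therefore holds for equal under-counting, but not for every pattern of under-counting.

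**The case against.** The strongest reply is that a single word does the damage. Graft absorption is one of four imaging signs joined by *or*, so an alternative that cannot apply removes no events. The fixation item follows *with or without* and can be read as optional. Increased abscess, new sequestrum and worse bone destruction are all visible without surgery. Assessors who read the sentence as confirmation by CT or MRI would still count most painful, imaging-confirmed recurrences. This stands, and it means that the loss is of unknown size. It does not rescue the wording, because those assessors would be applying a rule that the article does not state.

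Several stronger readings are tempting, and the documents do not support them:

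- *No participant can ever have an event.* The Introduction says that mild cases are managed primarily, not exclusively, with drugs, and Table 2 does not exclude spinal surgery. Some participants may be operated on. A trial with no events at all would also be visibly uninterpretable rather than a quiet false positive.
- *The 14% and 39% estimate the trial's real error rate.* They follow from assumed capture rates. The literal reading would give almost no capture in unoperated participants, and the lenient reading little or no loss from this word.
- *The 5% planning rate is wrong for this endpoint.* The article places its justification in the Supplementary Material, which is not shown. It is unverified, not shown to be wrong.
- *Mandatory pain is part of the same error.* Requiring symptoms plus imaging is a defensible choice. Whether pain should be required, and how later surgery or re-treatment should count, are separate design questions.

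**Conclusion.** The point holds as a mismatch between the stated primary efficacy definition and the population it is applied to. The definition requires imaging after an operation that neither arm includes, and nothing is said about unoperated participants. This is not detail left to a fuller document: the article states an operative rule, and the rule does not fit.

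The consequence is an endpoint that is either unattainable for an unoperated participant or interpreted site by site. With equal under-counting the bias is towards non-inferiority, and the illustrative false-positive rate moves from 5% to about 14% (75% capture) or 39% (50% capture). That result rests on assumed capture, equal capture in both arms, true rates of 5% v 11.6%, and 135 evaluable per arm. With unequal capture the bias may be larger or may reverse. The calculated sample size is unaffected.

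**What to change.** Reword the definition in Primary outcomes:

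1. Delete *postoperative*.
2. State that the fixation and graft signs apply only to participants who have had spinal surgery.
3. Require confirmation by spinal CT or MRI showing increased abscess, new sequestrum or aggravated bone destruction compared with the participant's previous spinal scan, applied identically in both arms.
4. Reconcile this with Table 4 by naming the comparator. Spinal imaging is implied elsewhere: Table 2 bases the diagnosis partly on radiological examination, and clinical cure in Secondary outcomes has a radiological component. The protocol should say which existing scan, diagnostic or end-of-therapy, serves as the reference.
5. Confirm that the 5% planning rate refers to the reworded endpoint.

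The cost is a change of wording in the protocol, CRF and SAP, and recording of the comparator scan. If no such scan is in fact obtained from every participant, Table 4 would also need a spinal imaging entry, which is a real added cost. No extra participants are needed. Because the trial is open-label, the change should be made before recurrences are assessed.
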